## 7.4 Gene expression profile

(1) Liver biopsy

Perform liver biopsy to collect liver tissue samples for determinations of the liver gene expression profile drug concentrations.

[1] Liver biopsy procedure

Perform liver biopsy after the absence of the risk of haemorrhage has been confirmed in advance by the blood coagulation test, etc. Under local anesthesia, needle biopsy is performed with the aid of ultrasonography using a Bard Monopty automatic biopsy needle (Max Core). The specification is as follows: depth of insertion; 22 mm, external diameter; 16 G, needle length; 160 mm. The upper limit for the amount of liver tissue samples to be collected per day for determination of the gene expression profile and drug concentrations in the liver will be 20 mg, respectively. The patients will remain at rest for a while after liver biopsy. They will be hospitalized on the days of examination.

[2] Timing of liver biopsy and the acceptable range

On the day before the start of study drug administration and on the day of evaluation at Week 8 after the start of administration (4 hours after administration)

- 4 hours after administration: ±30 minutes

If a deviation from the designated timing of sample collection is within the acceptable range, the sample will be deemed as collected at the designated timing.

If the investigator or the subinvestigator deems that liver biopsy cannot be performed on the designated day of evaluation at Week 8 due to the subject’s health condition, the liver biopsy can be postponed by up to 28 days. In such cases, the period of Step I [the period of administration of two doses, i.e., 300 mg/day (twice daily) and 600 mg/day (twice daily)] will be extended until completion of liver biopsy.

[Rationale for timing of liver biopsy]

The rationale for the timing of liver biopsy is described, as the rationale for selection of the administration period for determination of the gene expression profile, in the section of “Rationale” under “4.4.(3) Study drug administration period” for determination of the gene expression profile.

From the results of the phase I single administration study, the appropriate timing of liver biopsy on the day of evaluation at Week 8 of study drug administration was deemed to be 4 hours after administration, which is close to the time point of the Cmax of unchanged NIK-333.

(2) Determination of the gene expression profile in the liver

The details of the procedure of determination of the gene expression profile are described in the “Manual for determination of the gene expression profile of NIK-333.”

[1] Procedure for specimen processing

Collect a liver tissue sample and remove blood using a piece of physiolocial saline-soaked filter paper. Then transfer the sample to a sample tube containing RNAlater (Ambion) and immerse it in the solution at 4C at least for a night. Take the liver tissue sample out from the RNAlater within 3 days, transfer it to a new sample tube, and preserve in liquid nitrogen. After that, subject the liver tissue sample to RNA extraction and purification within 14 days, and then freeze and store at -80C until determination of the gene expression profile.

[2] Determination of gene expression profile in the liver

The gene expression profile in the liver tissue will be determined before and after administration of NIK-333 using the microarray of Kanazawa University (KANAZAWA Liver Chip 10K).

Subject genes shown by the above analysis to be potential drug response genes to further analysis by the Real-Time RT-PCR method.

[3] Preservation and disposal of the specimens after determination of the gene expression profile

Store the RNA samples remaining after determination of the gene expression profile at the facility undertaking determination and analysis of gene expression profile (Disease Control and Homeostasis, Graduate School of Medicine, Kanazawa University) until the day when 5 years have passed after the date of manufacturing approval for a drug related to the study drug concerned (or 3 years after the day on which discontinuation of development is decided, if development of the drug is discontinued) or until the day of completion of re-examination, which ever later. At the end of the storage period, the study investigator of the facility undertaking determination and analysis of gene expression profile will discard the samples concerned.

(3) Determination of the gene expression profile in peripheral blood

[1] Timing of blood sample collection and the acceptable range

On the day before the start of study drug administration and on the day of evaluation at Week 8 after the start of administration (4 and 8 hours after administration).

- 4 hours after administration: ±30 minutes

- 8 hours after administration: ±30 minutes

[Rationale for timing of blood sample collection]

Blood samples for determination of the gene expression profile in peripheral blood will be collected 4 hours after study drug administration, the same timing as determination of the gene expression profile in the liver. The blood samples for determination of the gene expression profile in peripheral blood will also be collected 8 hours after administration to monitor the time-course change of the gene expression profile after study drug administration. The timing of 4 hours after study drug administration is close to the time point of the Cmax of unchanged NIK-333, and the timing of 8 hours after study drug administration corresponds with the elimination phase of unchanged NIK-333 and which is close to the time point of the Cmax of NIK-333 lipids form.

[2] Procedure for specimen processing

Collect blood samples using the PAXgene Blood RNA vacuum blood collection tube (2.5 mL×2). Extract, purify and concentrate RNA using the PAXgene Blood RNA Kit (QIAGEN). Then, freeze and store samples at -80C.

[3] Shipment of the specimens

The study center will send the RNA samples in the frozen state to the facility undertaking determination of the gene expression profile in peripheral blood. The quality of RNA samples after shipment will be confirmed using a bioanalyzer at the facility undertaking determination of the gene expression profile in peripheral blood.

[4] Determination of the gene expression profile in peripheral blood

The gene expression profile in peripheral blood will be determined before and after administration of NIK-333 using AceGene®Premium (DNA Chip Research Inc.).

Subject genes shown by the above analysis to be potential drug response genes to further analysis by the Real-Time RT-PCR method.

[5] Preservation and disposal of the specimens after determination of the gene expression profile

Handle the RNA samples extracted from peripheral blood in the same way as the RNA samples extracted from the liver tissue as described in the section of “7.4 (2), [3] Preservation and disposal of the specimens after determination of the gene expression profile.”

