NIK-333 exhibits a transcriptional action via the retinoic acid receptor (RAR) and retinoid X receptor (RXR), a differentiation-inducing action against HL-60 cells (human acute promyelocytic leukemia-derived cells), and retinoid-like actions. Moreover, NIK-333 induced apoptosis in well-differentiated human hepatoma-derived cells, HuH-7, although such an action was not seen for all-trans-RA and 9-cis-RA. It also significantly inhibited rat hepatocarcinogenesis by 3'-MeDAB and DEN15). The mechanisms of hepatocarcinogenesis hypothesized to date include a possibility that, when hepatitis persists and necrosis and growth of hepatocytes are repeated, mutation is induced and the cells grow without being eliminated by apoptosis, thereby leading to carcinogenesis.16) In contrast, NIK-333 is presumed to inhibit hepatocarcinogenesis on the basis of the following mechanisms: (1) elimination of preneoplastic cells or unapparent cancer cells in the liver by the apoptosis-inducing action, and (2) the antitumor effect and the carcinogenesis-inhibiting effect brought about by the differentiation-inducing action. Moreover, NIK-333 has recently been found to have an action to inhibit genetic transformation and an action to inhibit growth,15） and these actions are considered to be involved in the cancer-inhibiting effect and the anti-promotion effect.

2) Information regarding gene expression

Reported effects of NIK-333 on gene expression include promotion of cell-cycle controlling protein p21 through RAR- activation in human hepatoma-derived cells, inhibition of cell growth by inhibition of cyclin D,17) and induction of apoptosis via the inhibition of TGF-18).

Moreover, the inhibitions of TGF- expression and hepatocarcinogenesis have been reported in the rat liver cancer model.15) In evaluating the usefulness of NIK-333 in the future, it is important to investigate whether the changes of gene expression observed in these basic studies are also seen in clinical settings.

[3] Clinical studies

1） Safety

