# 7. Examination and observation parameters

## 7.1 Procedures of subject registration

(1) Informed consent and definite diagnosis

[1] Informed consent from the subjects

The investigator or the subinvestigator will evaluate patients who have undergone topical medical therapy or surgical resection, and obtain informed consent in writing from those patients deemed eligible to participate in this study.

[2] Confirmation of eligibility of the subjects

After an informed consent has been obtained from a subject, the investigator or the subinvestigator will perform the scheduled dynamic CT and various tests to confirm complete cure within 56 days before registration, and will confirm that the subject satisfies the inclusion criteria and does not fall under any exclusion criteria.

[Test parameters regarding the inclusion criteria and exclusion criteria]

1） Dynamic CT images

2） Medical examination (symptoms/signs)

3） Blood pressure (dorsal position or sitting position)

4） Child Pugh classification

(Liver encephalopathy, ascites, serum bilirubin, serum albumin and prothrombin time)

5) HCV-RNA tests (quantitative)

6) HBs antigen tests (qualitative)

7） HCG tests (pregnant or not: premenopausal women only)

8） Hematology tests (platelet count, hemoglobin level)

(2) Subject registration

The investigator or the subinvestigator will enter necessary information on the subject registration form and will fax it to the subject registration center. The sponsor will confirm on the subject registration form received (Fax) that there are no problems in the eligibility of the subjects.

(3) Study drug assignment and start of study drug administration

The investigator or the subinvestigator will start administration of the study drug according to the assignment table prepared in advance.

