Take body temperature (axillary), blood pressure (systolic/diastolic), pulse rate (dorsal position or sitting position) and body weight at 4-week intervals from the start of study drug administration (within 14 days before the start of administration) until the end of study drug administration, and at the time of follow-up examination.

If the study has been discontinued, body temperature (axillary), blood pressure (systolic/diastolic), pulse rate (dorsal position or sitting position) and body weight will be determined to the extent possible.

[6] Laboratory tests

Collect blood and urine samples and determine the following parameters at 4-week intervals from the start of study drug administration (within 14 days before the start of administration) until the end of study drug administration, and at the time of follow-up examination.

If the study has been discontinued, blood and urine samples will be collected and the following parameters will be determined to the extent possible.

1) Hematology tests: White blood cell count, red blood cell count, hemoglobin level, hematocrit, platelet count

2) Blood biochemistry tests: Total protein, serum albumin, serum bilirubin, total cholesterol, LDL cholesterol, HDL cholesterol, triglyceride, blood glucose, urea nitrogen, Cl, Na, K, Ca, ALP, AST (GOT), ALT (GPT), LDH, -GTP, choline esterase, serum creatinine, A/G ratio, free fatty acid, 2-microglobulin

3) Urinary tests (fresh urine): Qualitative (glucose, protein, urobilinogen, ketone body, occult blood), urinary albumin (converted to creatinine), urinary sediment (red blood cells, white blood cells, epithelial cells, casts, others), 2-microglobulin

[7] Blood pressure parameters

Collect blood and urine samples and determine the following parameters at 48-week intervals from the start of study drug administration until the end of study drug administration. If the systolic blood pressure exceeds 140 mmHg or the diastolic blood pressure exceeds 90 mmHg on two or more successive measurements, blood pressure parameters will be determined at the time of second or subsequent examination. However, determination of creatinine clearance, one of the blood pressure parameters, under increased blood pressure will be conducted to the extent possible.

1) Blood biochemistry tests: Renin activity, aldosterone, cortisol, uric acid, FT3, FT4, TSH, angiotensin II, hANP, BNP, catecholamine, growth hormone, dehydroepiandrosterone sufate (DHEAS)

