## 12.2 Analysis of gene expression profile

Compare the data on gene expression profile obtained before and after the study drug administration (days of evaluation at Week 0 and Week 8) by dose (300 mg/day and 600 mg/day) and by patient. The details about the method of analysis of the gene expression profile are presented in the “Manual for determination of the gene expression profile of NIK-333.”

It may become necessary to make additional analyses focused on the NIK-333 response gene on the basis of the results of the present analysis of gene expression profile. In such cases, revise the “Manual for determination of the gene expression profile of NIK-333.”

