| Child-Pugh classification | Liver encephalopathy, ascites, serum bilirubin, serum albumin, prothrombin time |
| HCV-RNA | Quantitative |
| HBs antigen | Qualitative |
| HCG tests | Pregnant or not (premenopausal women only) |
| Hematology tests | Platelet count, hemoglobin level |

*: Menopausal status and whether or not being pregnant will be confirmed for female subjects.

Table 2 Examination, observation and evaluation parameters during the study drug administration period (including the day of the start of administration)

| Examination parameters | Examination, observation and evaluation parameters |
| --- | --- |
| Gene expression analysis | Gene expression profile in the liver and peripheral blood |
| Exploratory biomarker | TGF- concentration in plasma (biomarker associated with gene expression) |
| Pharmacokinetics | Drug concentrations in the liver, plasma and urine  (unchanged NIK-333 and NIK-333 lipids form) |
| Abdominal imaging/  diagnosis | Presence or absence of HCC on dynamic CT, US, and MRI images |
| Medical examination | Symptoms*, signs |
| Vital signs, etc. | Body temperature (axillary), blood pressure (systolic/diastolic: dorsal position or sitting position), pulse rate (dorsal position or sitting position), body height#, body weight |
| HCV-RNA | Quantitative (including genotype analysis#) |
| HCG tests | Pregnant or not (premenopausal women only) |
| Hematology tests | White blood cell count, red blood cell count, hemoglobin level, hematocrit, platelet count |
| Blood biochemistry tests | Total protein, albumin, bilirubin, total cholesterol, LDL cholesterol, HDL cholesterol, triglyceride, blood glucose, urea nitrogen, Cl, Na, K, Ca, ALP, AST, ALT, LDH, -GTP, choline esterase, serum creatinine, A/G ratio, free fatty acid, 2-microglobulin |
| Blood pressure parameters | Blood biochemistry tests: Renin activity, aldosterone, cortisol, uric acid, FT3, FT4, TSH, angiotensin II, hANP, BNP, catecholamine, growth hormone, dehydroepiandrosterone sufate (DHEAS)  Urinary tests (accumulated urine): creatinine clearance |
| Tumor markers | AFP，AFP-L3，PIVKA-II |
| Fibrosis marker | Hyaluronic acid |
| Urinary tests (fresh urine) | Qualitative (glucose, protein, urobilinogen, ketone body, occult blood)  urinary albumin (converted to creatinine), urinary sediments (red blood  cells, white blood cells, epithelial cells, columnar cells, others)  2-microglobulin |
| Bone densitometry (DXA) | Bone density of lumbar vertebrae (L2 to L4) |

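### Blood expression is measured on unseparated blood with no white-cell differential, so a change in leukocyte mix between baseline and Week 8 could not be directly told apart from a drug response

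*Protocol*

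**What the plan says.** **Specimen.** Section 7.4 (3) has blood drawn into RNA-stabilising tubes: "Collect blood samples using the PAXgene Blood RNA vacuum blood collection tube (2.5 mL×2". The next step is "Extract, purify and concentrate RNA using the PAXgene Blood RNA Kit (QIAGEN". No isolation or sorting of leukocytes is described. The protocol does not use the term whole blood, but this tube and kit with no separation step amount to it.

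**Sampling times.** Blood for expression is taken on the day before treatment starts, with no clock time, and at Week 8 at 4 h and 8 h after the dose (each ±30 minutes). Liver biopsies take place on the same two days, the second one at 4 h after the dose.

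**Analysis.** Section 12.2 says: "Compare the data on gene expression profile obtained before and after the study drug administration", by dose and by patient. Both groups receive drug. The detailed method is left to a separate manual. Candidate genes go to a second step: "Subject genes shown by the above analysis to be potential drug response genes to further analysis by the Real-Time RT-PCR method".

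**Haematology.** Section 7.5 (1)[6] lists "Hematology tests: White blood cell count, red blood cell count, hemoglobin level, hematocrit, platelet count". Table 2 repeats the same five items ("White blood cell count, red blood cell count, hemoglobin level, hematocrit, platelet count"), and Table 3 has them again for follow-up. Registration has less: "Hematology tests (platelet count, hemoglobin level". No white-cell differential appears in any list.

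**Windows.** Under section 7.8, baseline haematology may be up to 14 days before the start. At Week 8 it falls under the 7-day window for other parameters, while expression has +28 days.

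**The concern.** An array value from unseparated blood is a weighted average: expression per cell in each leukocyte type, weighted by that type's share of the cells. The study wants the first factor, a gene whose transcription responds to NIK-333. The array returns both factors combined, and the second is not measured.

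If the mix differs between baseline and Week 8, genes characteristic of one lineage move together and look like a coherent drug signature. Three features of the plan leave this open:

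- There is no untreated group to show what happens without drug. Comparing 300 mg with 600 mg does not help if the shift is common to both doses or itself dose-related.
- RT-PCR measures abundance in the same kind of RNA, so it would confirm the change whatever its cause.
- A shift need not come from the drug. The baseline sample has no clock time, whereas the Week 8 samples are tied to the dose. The 8 h sample also follows a liver biopsy, although section 7.4 (3) uses it to follow the time course after the drug.

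At stake is the meaning of any blood response gene. Blood is one of the two tissues in which the study seeks such genes.

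**Working it through.** The plan gives no figure to reproduce: 6 subjects per group is set by feasibility (section 12.6), with no effect size, SD or error rate. The check has three parts.

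**1. Is the mix recoverable from the scheduled haematology?** No. A total count carries no information on proportions. It also need not be contemporaneous:

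- Baseline: haematology up to 14 days before the start against expression 1 day before gives a gap of up to 14 − 1 = 13 days.
- Week 8: haematology on the nominal day against expression at +28 days gives a gap of up to 28 days.
- 8 h sample and biopsy: biopsy at 4 h ± 0.5 h and blood at 8 h ± 0.5 h put the sample between 7.5 − 4.5 = 3 h and 8.5 − 3.5 = 5 h after the procedure.

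**2. How large could the apparent change be?** Let p0 and p1 be the share of one leukocyte class before and after, and r its expression of the gene relative to the other white cells. Expression per cell and the total white count are held constant. The apparent fold change is

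F = (p1·r + 1 − p1) / (p0·r + 1 − p0), which tends to p1/p0 for a gene expressed only in that class.

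Example: 30% to 40% with r = 5 gives (2.0 + 0.6)/(1.5 + 0.7) = 2.6/2.2 = 1.18. All fractions below are assumptions; the protocol gives none.

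| Share before → after | r = 5 | r = 20 | class-only gene | log2, class-only |
|---|---|---|---|---|
| 30% → 40% | 1.18 | 1.28 | 1.33 | +0.42 |
| 30% → 25% | 0.91 | 0.86 | 0.83 | −0.26 |
| 30% → 20% | 0.82 | 0.72 | 0.67 | −0.58 |
| 30% → 15% | 0.73 | 0.58 | 0.50 | −1.00 |

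**3. Would a shift of that size be noticed with so few subjects?** The protocol names no test, so take a paired t test at nominal two-sided 0.05 as an illustration. It has n − 1 degrees of freedom and noncentrality (d/SD)·√n. Here d is the composition-only log2 shift, common to all subjects, and the SD of the paired log2 differences is assumed to be 0.3 to 0.5. The probability of flagging the gene is:

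| d (log2) | n = 6 (SD 0.5 to 0.3) | n = 12 (SD 0.5 to 0.3) |
|---|---|---|
| 0.26 | 0.18 to 0.41 | 0.38 to 0.78 |
| 0.42 | 0.39 to 0.78 | 0.76 to 0.99 |
| 0.58 | 0.63 to 0.96 | 0.95 to >0.99 |

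A stricter threshold would lower these figures. They show only that a moderate shift in mix, with an unchanged total count, is large enough to be picked up in this design.

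**The case against.** The other side has good arguments, and several of them stand.

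**Evidence that this drug shifts leukocytes is thin.** A reader might infer such a shift from section 2.2, which reports "a differentiation-inducing action against HL-60 cells (human acute promyelocytic leukemia-derived cells", and from white-cell decreases in phase I. The documents do not support that. Section 2.3 puts the EC50 for differentiation at 4.29 µmol/L. Section 4.4 gives mean single-dose peaks of 1.0 µM at 300 mg and 1.5 µM at 600 mg. A single intake in this trial is at most 4 × 75 = 300 mg, so the relevant peak is about 1.0/4.29 = 23% of that EC50. Plasma protein binding is 95% or more, and HL-60 is a leukaemia line, not circulating blood. The white-cell decreases are one event at 300 mg judged unrelated and one at 900 mg, a dose not used here. Both followed single doses, and the 48-week tables list none. A fall in total count is in any case not a change in mix. The point therefore rests on the sampling design, not on these data.

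**The arrays may carry some information.** A reader might infer that nothing collected could ever separate the two explanations. That goes too far. Lineage genes moving together would be visible in the arrays, the unseen manual could estimate cell mix from expression, remaining RNA is stored, and section 12.2 allows further analyses. What stands is that such an estimate is indirect, and neither 7.4 nor 12.2 mentions it.

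**Adjustment can remove a real effect.** If the drug acts by changing differentiation, the mix lies on its pathway. Requiring every gene to survive adjustment would over-correct. This stands and shapes the fix.

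**Scope.** The study is exploratory, the liver profile is untouched, and the fractions and SDs above are assumed. All of this stands.

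**Conclusion.** The point holds as a conditional one. If leukocyte proportions differ between the baseline and Week 8 samples, from whatever cause, lineage-specific genes would appear as blood response genes. RT-PCR would not expose this, and the protocol collects no direct measure that could. On assumed shifts in lymphocyte share of 5 to 10 percentage points from 30%, the apparent change in a lymphocyte-only gene is 0.67- to 1.33-fold, and smaller for genes that are only enriched in that class.

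It does not follow that a shift will occur, or that blood findings will be false. Nor does it bear on the liver profile. A differential is data collection: a mix not counted at the draw cannot be counted afterwards, so this is not a detail to leave to a later analysis plan. It is a worthwhile and inexpensive improvement to an exploratory blood analysis, not an error that undermines the study.

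**What to change.** - **Collect.** In section 7.5 (1)[6] and Table 2, add a white-cell differential on blood drawn with each expression sample: the day before the start, and Week 8 at 4 h and 8 h. It should follow the expression sample if the Week 8 biopsy is postponed.
- **Analyse.** In section 12.2, report blood expression changes with and without adjustment for the change in neutrophil or lymphocyte fraction. Use the comparison as a sensitivity screen that marks genes explainable by cell mix. Do not make survival of the adjustment a condition for naming a response gene.
- **Keep the model small.** Adjusting a within-dose mean change for both fractions leaves 6 − 3 = 3 residual degrees of freedom. One fraction leaves 6 − 2 = 4. Pooling the doses with a dose term and one fraction leaves 12 − 3 = 9. Use one fraction, or pool.

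**Cost.** A routine test at three time points and a little more blood. Existing scheduled haematology cannot be relied on for this, but blood is already drawn at all three times for expression and plasma drug levels, so no extra visit is needed. The added volume should go into the table in section 4.8. The adjusted results will be imprecise and should be presented as such.
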